#### Difference between expected weight loss and observed weight loss

Observed weight loss will be calculated based on the difference in body weight from baseline to follow-up. Expected weight loss will be calculated using two methods. The first method assumes that 1 kg of weight represents 7,700 kcal of energy. Calories expended during supervised exercise is divided by 7,700 kcal to derive expected weight loss (exercise energy expenditure divided by 7,700 kcal/kg) [33]. The second method is based upon more recent research which demonstrates that a 7,700-kcal deficit does not always produce a 1 kg of weight loss, because this formula overestimates weight loss [34-36]. The researchers who produced this body of work developed a more accurate model that accounts for the dynamics of weight change during exercise. This dynamic formula will be used to calculate expected weight loss, given the two different doses of exercise, and the accompanying observed weight loss. Weight loss difference will then calculated as observed weight loss minus expected weight loss [33].

### Secondary study outcome measures

#### Resting metabolic rate

Indirect calorimetry will be used to measure RMR on day −14 and day 160. Energy expenditure will be adjusted for change in BMI, as outlined by Martin *et al*. [37,38]. Each participant’s resting metabolism will be measured over a 30-minute period after a 12-hour overnight fast using a MAX-II metabolic cart system (AEI Technologies, Pittsburgh, PA, USA). After the participant has quietly rested for 30 minutes, a transparent plastic hood connected to the cart will be placed over the participant’s head. For the duration of the test, the participant will be asked to remain motionless and awake. Prior to each measurement, the pneumotach flowmeter will be calibrated using a 3-L calibration syringe (Hans Rudolph Inc, Shawnee, KS, USA), and gas analyzers will be calibrated using standardized gas mixtures. The inspired gas samples will be diluted by flow adjustment to maintain a carbon dioxide concentration between 0.7% and 0.9%. Oxygen uptake and carbon dioxide production will be calculated using M-II software. The average of the last 20 minutes of the measurement will be used to calculate RMR using Weir equations [39].

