**Methods/Design:**

E-MECHANIC is a three-arm, 6-month randomized (1:1:1) controlled trial. The two intervention arms are exercise doses that reflect current recommendations for (1) general health (8 kcal/kg body weight per week (8 KKW), about 900 kcal/wk) and (2) weight loss (20 KKW, about 2,250 kcal/wk). The third arm, a nonexercise control group, will receive health information only. The sample will include a combined total of 198sedentary, overweight or obese (body mass index: ≥25 kg/m^2^ to ≤45 kg/m^2^) men and women ages 18 to 65 years. The exercise dose will be supervised and tightly controlled in an exercise training laboratory. The primary outcome variables are energy intake, which will be measured using doubly labeled water (adjusted for change in energy stores) and laboratory-based food intake tests, and the discrepancy between expected weight loss and observed weight loss. Secondary outcomes include changes in resting metabolic rate (adjusted for change in body mass), activity levels (excluding structured exercise) and body composition. In an effort to guide the development of future interventions, the participants will be behaviorally phenotyped and defined as those who do compensate (that is, fail to lose the amount of weight expected) or do not compensate (that is, lose the amount of weight expected or more).

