### Study design and objectives

The E-MECHANIC study is a three-arm, 6-month randomized controlled trial (RCT). The selected exercise doses reflect current recommendations for (1) general health (8 kcal/kg body weight/wk (8 KKW), or approximately 800 to 1,000 kcal/wk) and (2) weight loss (20 KKW, or approximately 2,000 to 2,500 kcal/wk) [14]. A nonexercise control group will also be included in the study.

The primary objectives of the E-MECHANIC trial are (1) to test whether energy intake increases in response to either or both of two doses of exercise (8 KKW vs. 20 KKW), (2) to test whether the discrepancy between observed and expected weight loss (Wt Loss_diff_) differs between the two exercise groups (8 KKW vs. 20 KKW) and between the control and 20-KKW groups and (3) to determine whether change in energy intake mediates Wt Loss_diff_.

The secondary objectives of the trial are (1) to determine whether change in resting metabolic rate (RMR; adjusted for change in body mass index (BMI)) and activity levels (excluding structured exercise) differ across treatment groups; (2) to determine whether change in body composition differs by exercise dose; and (3) to characterize participants who compensate (that is, fail to lose the amount of weight expected) and compare them with those who do not compensate (that is, lose the amount of weight expected or more).

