#### Body composition

Measures of body composition, including fat and lean mass, will be assessed by dual-energy X-ray absorptiometry (DXA) (Lunar iDXA with Encore software version 13.60; GE Healthcare, Madison, WI, USA) at baseline (day −14 and day 0) and week 24 (day 160 and day 174). Lean mass measurements taken with DXA are used to adjust RMR for alterations in body composition [37]. Measurement data from DXA recordings will also be used to explore whether fat or fat-free mass changes differ between treatment groups and between compensators and noncompensators. The use of DXA involves minimal X-ray exposure—about the same as 12 hours of background radiation from the sun.

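### The adjuster for RMR change is contradictory (body mass or BMI in three places, DXA lean mass in a fourth), and the BMI rule can bias the arm comparison if fat and lean change differ between arms

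*Protocol article*

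**What the plan says.** The protocol article states the adjustment of RMR change in four places:

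- Abstract, Methods/Design: "Secondary outcomes include changes in resting metabolic rate (adjusted for change in body mass", so the adjuster is body mass.
- Study design and objectives, first secondary objective: "to determine whether change in resting metabolic rate (RMR; adjusted for change in body mass index (BMI)) and activity levels", so the adjuster is BMI.
- Secondary study outcome measures, Resting metabolic rate: "Energy expenditure will be adjusted for change in BMI", again BMI, with references 37 and 38 cited for the method.
- Secondary study outcome measures, Body composition: "Lean mass measurements taken with DXA are used to adjust RMR for alterations in body composition", so the adjuster is DXA lean mass, with reference 37 cited.

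The Data analysis section names age and baseline assessments as examples of covariates that may be kept in the final models. It does not say which body-size or composition measure applies to RMR.

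On timing, "Indirect calorimetry will be used to measure RMR on day −14 and day 160". The Body composition section and Table 1 put DXA on those two days as well (and on days 0 and 174). Table 1 lists height at screening only.

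**The concern.** A fall in RMR is one of the explanations that the Background lists for the shortfall in weight loss, and the Abstract asks whether energy expenditure outside structured exercise declines. To test this, the analysis must separate a change in metabolism from the change in RMR that simply follows from carrying less or different tissue. The adjuster makes that separation, so it determines what the adjusted outcome means.

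Two things are at stake. First, the article supports two different adjusted outcomes, and a choice between them could be made after the results are known. Second, the rule in the outcome definition uses BMI, which counts a kilogram of fat and a kilogram of lean tissue alike. If the arms differ in how their fat and lean mass change, and if the two tissues carry different RMR per kilogram, part of that composition difference remains in the adjusted RMR and looks like a treatment effect. Whether composition change differs by dose is itself one of the trial's secondary objectives, so the plan leaves open the very condition that matters here.

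**Working it through.** **Is there a figure to reproduce?** No. RMR is not in Table 3, and the article gives no RMR variance, effect size, tissue slope or expected composition change. The contradiction is established from the text. The arithmetic below is only an illustration of what the choice can do.

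**Step 1: how many adjusters are there?** The wording gives three: body mass, BMI and lean mass. With height measured once, BMI change is weight change divided by a constant for each participant. A 2-kg change is 2/1.55² = 0.83, 2/1.65² = 0.73 and 2/1.80² = 0.62 kg/m² at heights of 1.55, 1.65 and 1.80 m. BMI and body mass therefore carry nearly the same information, and the material conflict is two-way: mass or BMI against lean mass.

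**Step 2: when does each adjuster mislead?** Notation:

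- β_L, β_F: RMR slopes per kg lean and per kg fat.
- d_L, d_F: between-arm differences in lean and fat change.
- s_L, s_F: within-arm SDs of those changes, taken as independent.

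Suppose there is no true group effect beyond composition. The spurious group effects are then:

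- Body-mass change as covariate: (β_L − β_F)(d_L·s_F² − d_F·s_L²)/(s_L² + s_F²).
- Lean change alone as covariate: β_F·d_F.
- Lean and fat change together: 0.

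The first is zero if the slopes are equal or if the arms do not differ in composition change. Otherwise its sign depends on the pattern of change.

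**Step 3: illustration, every input assumed.** Take s_L = 1.0 kg and s_F = 2.5 kg, so s_L² + s_F² = 7.25.

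- β 20/4, d_L = +1, d_F = −3. Mass: 16 × (6.25 + 3)/7.25 = +20.4. Lean alone: 4 × (−3) = −12.
- β 25/3, d_L = +1, d_F = −3. Mass: 22 × 9.25/7.25 = +28.1. Lean alone: 3 × (−3) = −9.
- β 25/3, d_L = −0.5, d_F = −1.5. Mass: 22 × (−3.125 + 1.5)/7.25 = −4.9. Lean alone: 3 × (−1.5) = −4.5.
- β 20/20, d_L = +1, d_F = −3. Mass: 0. Lean alone: 20 × (−3) = −60.

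A simulation with the same SDs, 200,000 participants per arm, residual SD 80 kcal/day and height 1.68 m (SD 0.09) also covers BMI. Its sampling error is about 80 × √(2/200,000) = 0.25 kcal/day. Spurious group effects in kcal/day (truth 0):

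| β_L / β_F | d_L, d_F (kg) | BMI | Body mass | Lean only | Lean + fat |
|---|---|---|---|---|---|
| 20 / 4 | 0, −2 | 4.5 | 4.7 | −7.6 | 0.3 |
| 20 / 4 | +1, −3 | 20.3 | 20.4 | −12.1 | 0.0 |
| 25 / 3 | +1, −3 | 28.2 | 28.3 | −8.7 | 0.2 |
| 25 / 3 | −0.5, −1.5 | −4.9 | −4.7 | −4.3 | 0.1 |
| 13 / 5 | +1, −3 | 9.9 | 10.0 | −15.0 | 0.1 |
| 20 / 20 | +1, −3 | −0.7 | −0.1 | −60.0 | −0.2 |
| 20 / 4 | 0, 0 | −0.4 | −0.4 | −0.4 | −0.4 |

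Across all scenarios with unequal slopes and differing composition change, BMI and body mass each gave about −5 to +28, lean alone about −4 to −15, and lean plus fat about 0. BMI and body mass never differed by more than about 0.6 kcal/day. With equal slopes, lean alone gave about −30 to −60 wherever fat change differed between arms.

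**The case against.** The strongest reply is that this is loose wording in a condensed article. The Body composition section shows that the investigators recognise the composition problem and collect the data to handle it, and the exact model belongs in the full protocol or analysis plan. It is true that the article does not amount to a settled decision to ignore composition, and a missing model specification would be no finding. But the article does not leave the rule out. It states it four times, and the statements disagree.

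One might also read the adjusters as complementary. If mass change and lean change were entered together, fat change would be nearly recovered by subtraction and the difficulty would largely go away. No section says they are used together.

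A reader might infer more than the document supports:

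- *That BMI adjustment does bias the test and hides metabolic compensation.* This needs a between-arm difference in composition change and unequal slopes. The article gives neither, and its objective on body composition is an open question, not an expectation. The illustration shows errors in both directions, and none when either condition fails.
- *That three distinct adjusters compete.* In effect there are two.
- *That the lean-mass rule is the safe one.* It is not, if fat change differs between arms.
- *That one source is being cited for two incompatible methods.* The BMI statement cites references 37 and 38 and the lean-mass statement cites 37. What each prescribes cannot be checked from the article.

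**Conclusion.** The contradiction stands: body mass or BMI in the Abstract, the secondary objective and the outcome definition, against DXA lean mass in the Body composition section, with Data analysis silent. The stated BMI rule can bias the between-arm RMR comparison, on two conditions: fat and lean changes differ between arms, and their RMR slopes differ. Neither sign nor size can be determined from the document. The range of about −5 to +28 kcal/day rests wholly on assumed slopes, SDs and composition changes, and with no RMR variance stated it cannot be turned into an effect on the test result. RMR is a secondary outcome, so sample size and the primary analyses are untouched. The inconsistency should be resolved before the RMR analysis is run.

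**What to change.** State one rule and use it in the Abstract, Study design and objectives, Resting metabolic rate and Body composition sections: RMR change is adjusted for both DXA fat-free mass and DXA fat mass. Name the same rule for RMR in Data analysis. Either of two forms would serve:

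- changes in fat-free and fat mass as covariates in the model for RMR change; or
- an equation fitted at baseline that predicts RMR from fat-free and fat mass, with arms compared on the change in measured minus predicted RMR.

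Fix the form in advance, and use the day −14 and day 160 scans so that composition and RMR come from the same days. Keep adjustment for BMI or body-mass change as a labelled sensitivity analysis.

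The cost is wording and analysis code only, with no added visit or measurement. The article reports the trial as still recruiting, and the data file is to be locked only after cleaning, so the rule can be set before any comparison is made.

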#### Activity level

SenseWear armbands will be used to measure physical activity and sedentary behavior at multiple time points throughout the study, including screening, the 2-week DLW period during baseline, week 4 and week 24. The armband is a small device that fits on the upper arm and has five types of sensors that continuously record data: a two-axis accelerometer, two galvanic skin response sensors, a heat flux sensor, a skin temperature sensor and a near-body temperature sensor. Body weight, height, handedness, age, sex and smoking status will be used in the calculation of energy expenditure, which will be carried out using proprietary software. The armband also records the length of time that it was worn on the body, which will allow us to detect noncompliance with data collection procedures. Activity data will be summated per day and displayed in 1-minute epochs, allowing data from days with poor compliance to be imputed or eliminated from the statistical analyses. Participants will be instructed to wear the armband 24 hours/day and remove it while showering, bathing or swimming. The participants randomized to one of the two exercise groups will be instructed to wear the armband during the exercise sessions. If the participant is <95% compliant with wearing the armband during screening or week 4 of testing, they will be asked to wear the armband for an additional 7 days. During the midpoint of baseline (day −7) and week 24 of testing (day 167), the participant’s armband will be checked for compliance. If found to be noncompliant, the participant will be counseled by study staff about the importance of wearing the armband as directed. Participants can be excluded prior to randomization for armband noncompliance.

#### Body composition

Measures of body composition, including fat and lean mass, will be assessed by dual-energy X-ray absorptiometry (DXA) (Lunar iDXA with Encore software version 13.60; GE Healthcare, Madison, WI, USA) at baseline (day −14 and day 0) and week 24 (day 160 and day 174). Lean mass measurements taken with DXA are used to adjust RMR for alterations in body composition [37]. Measurement data from DXA recordings will also be used to explore whether fat or fat-free mass changes differ between treatment groups and between compensators and noncompensators. The use of DXA involves minimal X-ray exposure—about the same as 12 hours of background radiation from the sun.

### Compensators and noncompensators

A secondary objective of the E-MECHANIC trial is to phenotype the behavior of participants in order to characterize compensators and noncompensators. This has been identified previously as an area in need of further study [9]. We carefully selected a battery of self-report instruments to comprehensively measure behavioral constructs associated with energy intake, body image, temperament and health-related quality of life. These questionnaires will be administered at baseline (day −14), week 4 (day 28), and week 24 (day 160). The measurement instruments described in the next two subsections will be used. All of them have been found to be reliable and valid.

#### Measurement of constructs associated with eating attitudes and behaviors

Visual Analogue Scales (VAS) are administered to measure subjective ratings of appetite [46]. Specifically, two forms of VAS data will be collected. First, a VAS will be completed by participants immediately before and after the food intake test meals. Second, retrospective VAS will be used to measure average ratings of satiety that participants experienced during the previous week. This method of collecting VAS data has been found to be consistent with daily assessments of satiety [47]. Supporting evidence for the reliability and validity of VAS data for measuring subjective states related to energy intake has been published [46].

The following instruments will be used to asses constructs associated with eating attitudes and behaviors: (1) the Multifactorial Assessment of Eating Disorders Symptoms (MAEDS), (2) the Eating Inventory (EI), (3) the Food Preference Questionnaire (FPQ), (4) the Food Craving Inventory (FCI) and (5) the Yale Food Addiction Scale (YFAS). The MAEDS is a 56-item measure of eating-disordered behavior that assesses depression, binge eating, purgative behavior, fear of fatness, restrictive eating and avoidance of forbidden foods [48,49]. The EI is designed to measure different dimensions of eating behavior, including cognitive restraint, disinhibition and hunger [48,49]. The FPQ is a self-report measure of food preference, including preference for sugars, complex carbohydrates, protein and fat [50]. The FCI is a measure of specific food craving and assesses the frequency with which an individual experiences craving for a particular food [51]. The YFAS is used to identify individuals who show tendencies toward addictive behaviors for certain types of food, such high-fat and high-sugar foods [52].

#### Measurement of constructs associated with physical activity and overall health

To measure constructs related to the propensity for physical activity and attitudes about general health, a number of valid questionnaires will be administered to participants. First, the tendency to participate in movement throughout the day will be assessed using the Activity Temperament Questionnaire [53,54]. Second, the Medical Outcomes Study 36-item Short Form will be used to measure mental and physical aspects of quality of life [55]. Third, sleep quality and disturbances over a 1-month interval will be assessed with the Pittsburgh Sleep Quality Index. Fourth, the Compensatory Health Beliefs Scale will be used to measure compensatory health-related beliefs, such as justifying eating an excessively large meal because one plans to exercise later in the day [56,57]. Fifth, body image and body dissatisfaction will be measured using the Body Morph Assessment (BMA) computer program [58]. BMA is a system that presents body silhouettes to participants. The body silhouettes range from very thin to very obese, and individuals being assessed manually increase or decrease the size of the silhouette by using a pointer on the computer screen. In this way, they indicate their current body size (CBS), ideal body size (IBS) and realistic body size (RBS). Two discrepancy scores (CBS − IBS and CBS − RBS) are derived as the differences between CBS and IBS and IBS.

#### Energy intake

The power analyses for the two methods by which energy intake will be measured rely on the effect sizes given in Table 3. The power analyses for energy intake, measured on the basis of DLW, indicate that the study will have a power of 0.93 for us to detect a 200-kcal difference in changes in energy intake between the 8-KKW and 20-KKW groups and between the control and 20-KKW groups. The study will also have 0.95 power for us to detect a 200-kcal difference in changes in energy intake measured with food intake tests in the laboratory between the 8-KKW and 20-KKW groups and between the control and 20-KKW groups.

#### Discrepancy between expected weight loss and observed weight loss

The effect sizes for the calculations and the power analyses are summarized in Table 3. They indicate that the study will have a power of 0.90 for the Wt Loss_diff_ comparisons.

### Data analysis

Analytic data will be archived in an electronic file. Prior to locking the file against further change, we will inspect all data for completeness, proper range and internal consistency. This data-cleaning process will include mock analyses by an analyst blinded to intervention group assignment. Any changes made will be documented in permanent records. Statistical analyses will be performed only after careful consideration is given to the assumptions underlying the statistical methods employed, using model diagnostics such as quantile plots of studentized residuals, component-plus-residual plots and examination of leverage points and outliers.

First, baseline participant characteristics (for example, age, sex, race, weight, BMI, waist circumference) will be summarized for each intervention group as counts and percentages for categorical variables and as means and 95% confidence intervals for continuous variables. The statistical significance of differential longitudinal changes in response to interventions will be assessed by employing repeated-measures mixed-effects models with maximum likelihood estimation and Kenward-Roger adjustment to the degrees of freedom of the relevant test statistic. The three interventions will be compared across assessment times (for example, baseline, week 4, week 24). Intervention, race, sex and assessment times will be taken as fixed effects. Participants within groups will be considered as having random effects. Covariates such as age and baseline assessments will be included in preliminary models and retained in the final analytic models if warranted. The model covariance structure (for example, unstructured, compound symmetric, autoregressive) across time will be investigated to enhance the efficiency of the statistical tests. The results for each outcome variable will be summarized as least-squares means and 95% confidence intervals for each intervention group across the assessment times. Model residuals will be tested to see if distributions are approximately Gaussian and data transformations (for example, logarithmic) will be performed if needed. Group differences in baseline characteristics will be tested, and corrective steps, such as poststratification and addition of model covariates, will be taken if necessary. Linear contrasts on least-squares means will be used to test pairwise differential mean changes in each outcome measure from baseline to subsequent assessment times between the three intervention groups. Null hypotheses will be tested against two-directional alternatives at the nominal 0.05 significance level using Tukey-Kramer–adjusted *P*-values when appropriate. All statistical analyses will be performed using SAS version 9.3 statistical software (SAS Institute, Cary, NC, USA).

Second, we will characterize compensators vs. noncompensators, where *compensators* will be defined as those who fail to lose the expected amount of weight during the exercise trial and *noncompensators* will be defined as those who meet or exceed the expected amount of weight loss during the trial. Differences between the groups on the following variables will be tested: (1) baseline values derived from self-report instruments, (2) baseline energy intake measures (for example, total kilocalories, macronutrient intake and fat and sugar intake) and (3) baseline activity levels (quantified by SenseWear armband readings). In addition, differences between compensators and noncompensators will be evaluated for sex and race disparities, and compensators and noncompensators will be compared with respect to changes in outcomes from baseline to week 24.

As an initial step in a mediator analysis, we will test whether changes in energy intake mediate or partially mediate the relationship between group assignment (exercise dose) and Wt Loss_diff_. We will follow the methods of Baron and Kenny [59] and determine whether Wt Loss_diff_ is predicted by group, with grouping variables coded as 8 KKW vs. 20 KKW and control vs. 20 KKW. Subsequently, we will test whether change in energy intake predicts Wt Loss_diff_. Assuming that the results are significant, we will then determine whether group significantly predicts Wt Loss_diff_ independently of energy intake. If group does not independently predict Wt Loss_diff_, then the relationship between group and Wt Loss_diff_ may be attributable to change in energy intake. That is, we will then conclude that change in energy intake mediated the relationship between group and Wt Loss_diff_. If the relationship between group and Wt Loss_diff_ is reduced after accounting for change in energy intake, then partial mediation will have been demonstrated.

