Researchers who have examined engaging in exercise for weight loss have found equivocal results showing less-than-expected changes in body weight, particularly when associated with high doses of exercise, with relatively higher interindividual and between-sexes variability [7]. The mechanisms responsible for the failure of exercise to produce substantial weight loss in most, but not all, individuals need to be elucidated. A better understanding of the mechanisms responsible for this compensation is critical to developing strategies to optimize the health benefits associated with exercise [8]. Blundell *et al*. noted that a large amount of variability in the degree to which people increase energy intake in response to exercise. Hence, people can be categorized as “compensators” and “noncompensators,” in this regard; yet, little is known about the characteristics of these groups or the mechanisms responsible for compensation [9]. In accord with this, King *et al*. emphasized the need to examine weight compensation in response to exercise and develop individualized interventions in order to prevent less-than-expected weight loss [10]. These researchers indicated that a fundamental criticism of engaging in exercise for weight loss is indeed the issue of compensation. The energy deficit caused by exercise is counteracted by compensatory behaviors, and thus weight control is hindered. These authors outlined the components of energy intake and expenditure that might volitionally or nonvolitionally change in response to exercise, including metabolic and behavioral factors. Furthermore, the authors reported that important limitations of the existing research include the short duration of exercise interventions, measurement of energy intake for short periods of time and difficulty in obtaining accurate measurements of energy intake and expenditure.

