After being screened into the trial, participants will complete the comprehensive baseline assessment and will be randomly assigned to one of the exercise arms (8 KKW or 20 KKW) or to the control group (nonexercise arm). Participants will be enrolled at a 2:1 female/male ratio and randomized separately to one of the three intervention groups at a 1:1:1 ratio to obtain an equal number of women and men in each treatment group. Participants who drop out (that is, fail to return for the 6-month examination) will not be replaced. Participants in the 8-KKW and 20-KKW intervention groups will continue to attend exercise sessions during week 4 and week 24 assessment periods. Participants who have not met the intervention energy expenditure goals by week 24 will be allowed to exercise up to 3 weeks after the week 24 assessment period.

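### Men and women are randomized separately, but a plain sex effect drops out of change-from-baseline contrasts, so outcomes modelled with baseline as a response make no use of the stratification (minor loss of precision)

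*Protocol article*

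**What the plan says.** **Randomization.** Assessments and schedule of procedures: "Participants will be enrolled at a 2:1 female/male ratio and randomized separately to one of the three intervention groups at a 1:1:1 ratio". With 198 participants this means 66 per arm, about 44 women and 22 men. Among the 60 completers per arm expected under Statistical power and sample size, it means about 40 and 20.

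**Model.** Data analysis plans "repeated-measures mixed-effects models with maximum likelihood estimation and Kenward-Roger adjustment to the degrees of freedom of the relevant test statistic", compares the arms over assessment times that include baseline, and continues: "Intervention, race, sex and assessment times will be taken as fixed effects". No interaction is written out.

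**Tests.** "Linear contrasts on least-squares means will be used to test pairwise differential mean changes in each outcome measure from baseline to subsequent assessment times".

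**Other adjustment.** "Covariates such as age and baseline assessments will be included in preliminary models and retained in the final analytic models if warranted". After a test of baseline differences between groups, "corrective steps, such as poststratification and addition of model covariates, will be taken if necessary".

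**Sex in the rationale.** The Background describes exercise studies of body weight as showing "relatively higher interindividual and between-sexes variability".

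**The concern.** When randomization is stratified, the arms are balanced on the stratum by design, and the treatment contrast is more precise than an unstratified one to the extent that the stratum predicts the outcome. The analysis shows that gain only if it removes the stratum's contribution from the residual variance of the quantity being tested.

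Here the quantity tested is a change. If baseline is one of the responses, a sex main effect describes how men and women differ in level at every visit. It says nothing about how they differ in change. Any sex difference in change then stays in the residual, and the reported standard errors, confidence intervals and P-values are wider or larger than the design warrants. What is at stake is some power and precision, not the validity of the comparison.

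**Working it through.** **1. The plan's own figure.** Table 3, energy intake by doubly labeled water: 60 per group, difference 200 kcal, SD 316, two-sided α 0.05. Effect size 200/316 = 0.633. Noncentrality 0.633 × √(60/2) = 3.47. Power is 0.930 by noncentral t (0.934 by the normal approximation), against 0.93 stated. The figure reproduces.

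**2. Why the sex term cancels.** Write the response of participant i in arm a at time t as

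Y(i,t) = μ(a,t) + β·sex(i) + person effect(i) + error(i,t).

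The change is Y(i,24) − Y(i,0) = μ(a,24) − μ(a,0) + error(i,24) − error(i,0). The term β·sex(i) has gone, so it can neither adjust the contrast nor reduce its residual variance. A sex-by-time term adds δ·sex(i) to the change, where δ is the sex difference in change, and so removes it from the residual.

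**3. Size.** Let p = 2/3 be the share of women, and g = δ in within-sex SDs of change. Without sex-by-time,

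variance of change = within-sex variance × [1 + p(1 − p)g²], with p(1 − p) = 2/9.

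The SE ratio is √(1 + 2g²/9). At g = 0.5 this is √1.0556 = 1.027.

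The article does not say whether SD 316 is a total or a within-sex SD, so both readings are shown. If it is the total SD and g is in total-SD units, the within-sex SD is 316 × √(1 − 2g²/9). At g = 0.5 this is 316 × 0.972 = 307.

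| Assumed sex difference in change, g | SE ratio, without/with sex-by-time (g in within-sex SD) | Power, 316 = total SD: without → with | Power, 316 = within-sex SD: without → with |
|---|---|---|---|
| 0.25 | 1.007 | 0.93 → 0.934 | 0.927 → 0.93 |
| 0.5 | 1.027 | 0.93 → 0.943 | 0.917 → 0.93 |
| 0.75 | 1.061 | 0.93 → 0.957 | 0.900 → 0.93 |
| 1.0 | 1.106 | 0.93 → 0.974 | 0.875 → 0.93 |

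At 0.5 total SD the unremoved share of variance is 2/9 × 0.25 = 5.6%, equivalent to about 0.056 × 180 = 10 completers.

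**4. Check by simulation** (40 women and 20 men per arm, within-sex SD of change about 1).

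- Mixed models with baseline in the response, g = 0.5, complete data, 25 replicates: mean SE of the arm-by-time contrast 0.1854 without sex, 0.1854 with a sex main effect, 0.1796 with sex-by-time. The point estimates were identical.
- The same with 10% missing at follow-up: 0.2009, 0.2002 and 0.1946. The main effect then helps only slightly, and estimates differ a little between models.
- Change as the single response with a sex main effect, complete data: SE 0.1796, the same as sex-by-time in the repeated-measures model.
- Type I error, complete data, 20,000 replicates: 0.045 at g = 0.5 and 0.031 at g = 1.0 when sex is left out of the change; about 0.050 in both when it is included.

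**The case against.** **The sentence is a list of factors, not a model statement.** It also leaves out intervention-by-time, without which the planned contrasts could not be formed. A full protocol or analysis plan, not shown, may contain sex-by-time. This stands in part. A reader might infer that the article rules the interaction out; it does not. But the change contrasts themselves imply intervention-by-time, whereas nothing in the section implies sex-by-time.

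**Wt Loss_diff is not affected.** This stands in full. It is observed minus expected weight loss, so it is already a change with no baseline value to cancel against, and the listed sex term adjusts it. A reader might infer a power loss for this primary outcome too; none arises.

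**Baseline may enter as a covariate.** Also correct. If follow-up or change is the response and baseline is only a covariate, the sex main effect adjusts the contrast. The article leaves that choice open and counts baseline among the assessment times. The corrective steps do not fill the gap: they follow a test of baseline differences between arms, and separate randomization makes a sex imbalance unlikely.

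**The sex difference is unsupported in size.** This stands. The Background cites a study in which men lost 5.2 kg and exercising women kept their weight. But prescribed doses differed by sex (3,300 and 2,200 kcal/wk), training lasted 16 months, and female controls gained weight. The relevant quantity is the sex difference in change averaged over the three arms, and the article gives none for energy intake, resting metabolic rate or activity.

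**The harm is conservative and small.** It is. A reader might infer biased estimates or excess false positives; the algebra and the simulation show neither.

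**Conclusion.** The point holds as a minor one, for outcomes analysed with baseline in the response: energy intake by both methods, resting metabolic rate, activity and body composition. For these the sex term as listed does essentially nothing for the tested contrast, and the precision offered by separate randomization is not shown in the standard errors. The loss is under 3% of the standard error for a sex difference in change up to 0.5 within-sex SD and about 11% at 1.0 SD; it is zero if the sexes change equally. These sizes rest on an assumed sex difference, a 2:1 sex ratio preserved within each arm, and equal within-sex variances.

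The stated doubly labeled water power of 0.93 is not shown to be wrong. If SD 316 is the total SD, it already describes the analysis without sex-by-time. Nor does the article leave sex unexamined: it plans to look at sex when comparing compensators with noncompensators.

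**What to change.** In Data analysis, state that sex-by-assessment-time is included in every model that has baseline among the responses, and that sex enters directly for Wt Loss_diff and for any analysis with baseline only as a covariate. The cost is one degree of freedom for outcomes measured at baseline and week 24, and two where week 4 is also measured, with about 180 completers. No change to the sample size, the visits or the planned contrasts is needed.
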